### Interventions

After informed consent is obtained, patients are equally randomized into one of two arms:*Experimental arm*. Patients in this arm are treated by a 16-week regime of imiquimod 5 % cream.*Standard arm*. Patients in this arm receive standard treatment by LLETZ.

Follow-up visits are anchored to the start of the treatment (either imiquimod or LLETZ). Cytological assessment will be performed by two independent trained cytology analysts, according to the Papanicolaou system. In case of inconsistent results, a consensus will be reached by discussion. The histopathological assessment of cervical biopsies will be performed by two independent pathologists according to national guidelines, based on the WHO guidelines. In case of inconsistent results, a consensus will be reached by discussion. CIN diagnosis will be based on evaluation of histological features concerned with differentiation, maturation and stratification of cells and nuclear abnormalities, in combination with p16 staining. In CIN 1 there is good maturation with minimal nuclear abnormalities and few mitotic figures. Undifferentiated cells are confined to the deeper layers (lower third) of the epithelium. Mitotic figures are present, but not very numerous. Cytopathic changes due to HPV infection may be observed in the full thickness of the epithelium. CIN 2 is characterized by dysplastic cellular changes mostly restricted to the lower half or the lower two-thirds of the epithelium, with more marked nuclear abnormalities than in CIN 1. Mitotic figures may be seen throughout the lower half of the epithelium. In CIN 3, differentiation and stratification may be totally absent or present only in the superficial quarter of the epithelium with numerous mitotic figures. Nuclear abnormalities extend throughout the thickness of the epithelium. Many mitotic figures have abnormal forms.

Patients in the experimental arm are treated with imiquimod 5 % cream during 16 weeks. Imiquimod 5 % cream is administered in a vaginal applicator, containing 12,5 mg of imiquimod (one sachet). The cream is administered three times per week. The cream is administered by patients themselves at night, before going to bed. A vaginal shower is performed in the morning in order to remove cream remainders. In case of mild systemic drug-related side effects, patients are offered a prescription for anti-inflammatory drugs (paracetamol or NSAID). In case of more severe or persistent systemic or severe local side effects (Common Terminology Criteria for Adverse Events grade 2 or higher), the frequency of imiquimod application is decreased to twice per week, and subsequently to once per week if side effects persist. Imiquimod treatment is discontinued if side effects are unacceptable to patients hereafter. Subjects should use adequate contraception in order to prevent pregnancy. Subjects should not have vaginal sexual intercourse from the time of application of the imiquimod cream until the vaginal shower the next morning. A control colposcopy with diagnostic biopsies is performed after 10 weeks to rule out disease progression. Biopsies are performed at the initial high-grade CIN lesion site and at any other suspect site, with a minimum of two. In case of progressive disease (defined as increase in lesions size with stable disease grade, higher disease grade or invasive disease), surgical excision is performed.

Treatment efficacy for the experimental arm is evaluated at 20 weeks follow-up, by colposcopy with diagnostic biopsies. Biopsies are performed by using a cervical biopsy specimen forceps (Aesculap ER055R), at the initial high-grade CIN lesion site and at any other suspect site, with a minimum of two. In case of persistent or progressive disease (> CIN 1), surgical excision is performed.

Patients in the standard treatment arm undergo LLETZ at short term (within 4 weeks after the diagnosis). Excision of the transformation zone and macroscopic lesions is performed by a monopolar loop electrode, under local anaesthesia. A summary of study interventions can be found in Fig. 1.

**Fig. 1 Fig1:**
[figure not shown]
Summary of study interventions

The imiquimod treatment period was set at 20 weeks, in order to realize adequate treatment efficacy of imiquimod, while minimizing the risk of progression of cervical dysplasia to invasive disease. Progression of CIN into cervical cancer is considered to be a slow process. The annual risk of progression of CIN 3 to invasive cervical cancer is estimated to be less than 1 % [17]. We identified ten studies in which patients with high-grade CIN underwent watchful waiting for a set period of time [4, 6, 7, 18–24]. A total of 637 patients were included either as a control group, receiving no treatment during 6 weeks to 15 months, or followed during the period between diagnosis and LLETZ. Three cases of invasive disease were identified: all occurred in the same study after 16 weeks of observation. The possibility of invasive disease already present at the initial colposcopy (due to biopsy error) cannot be excluded. Based on these results, we set the maximum treatment period at 20 weeks and we included an additional control colposcopy with diagnostic biopsies after 10 weeks. When no disease progression is detected during this colposcopy, the imiquimod treatment can be continued until the 20 weeks colposcopy.

### Sample size calculation

The sample size calculation was based on a regression rate of 73 % at 20 weeks follow-up after immunotherapy and a 95 % treatment efficacy of LLETZ. Using 80 % power and alpha = 5 %, the estimated sample size required is 42 women in both arms. Allowing for a withdrawal rate of approximately 20 %, 53 women will have to be recruited in each arm. Sample size calculations for the secondary outcome measures indicated that roughly 70 patients per treatment arm would be necessary. Although the sample size calculation should be based on the primary outcome measure, we decided to recruit a total of 140 patients (70 per arm).

### Randomization

Randomization is performed by the principal investigator to prevent selection and allocation bias, by use of a computerized randomization tool. Sampling is stratified according to the following age categories: 18–24, 25–39, and 40 years and older. Sampling will be stratified according to study centre.

### Data collection

Coded data are stored both on paper and in an electronic database. Collected data are stored in a digital case report form (CRF). Raw data is available only to the principal and coordinating investigator. The following data are recorded:

*Baseline*Patients characteristics: age, ethnical background, education, medical history, smoking, sexual behaviour.HPV genotyping.Histological biomarkers on biopsies of patients in the experimental arm: markers of lymphoproliferative response: CD4, CD8, CD25, CD138, fox p3; cell cycle markers: p16, Rb, p53, Ki67, CK 13, CK 14, IMP3.Quality of life.

*6 weeks follow-up*Adverse effects of imiquimod treatment: patient reported side effects and side effects noticed at clinical investigation.Adverse effects of LLETZ treatment: patient reported side effects, using a standardized report form.

*10 weeks follow-up*Treatment compliance: amount of applied doses of imiquimod, as documented by the study subject on a dose calendar.Histological presence and grading of CIN for the experimental arm.Adverse effects of imiquimod treatment: patients reported side effects and side effects noticed at clinical investigation.

*14 weeks follow-up*Adverse effects of imiquimod treatment: patients reported side effects and side effects noticed at clinical investigation.

*20 weeks follow-up*Treatment compliance: amount of applied doses of imiquimod, as documented by the study subject on a dose calendar.Histological presence and grading of CIN for the experimental arm.Adverse effects of imiquimod treatment: patients reported side effects and side effects noticed at clinical investigation.Quality of life for all patients.

*6, 12, 24 months follow-up*Cervical cytology outcomes for all patients, including HPV genotyping.Quality of life for all patients at 12 months follow-up

### Statistical methods

Logistic regression analysis will be used to evaluate treatment efficacy of imiquimod treatment, compared to LLETZ treatment. Covariates in this analysis are age at diagnosis, CIN grade, smoking and HPV-subtype. Analysis will be based on intention-to-treat protocol. A biomarker prediction model for adequate response to imiquimod treatment will be developed by backward logistic regression analysis of biomarkers based on likelihood ration tests. The prevalence and severity of side effects of imiquimod and LLETZ treatment will be presented as proportions and means with 95 % confidence intervals. Differences in the rates of overall side-effects and severe side-effects between the imiquimod and LLETZ arms will be tested with a chi-square test. Disease recurrence rates after 6, 12 and 24 months will be evaluated in successfully treated patients by use of multiple logistic regression analysis, after adjustment for age at diagnosis, CIN grade, smoking, sexual behaviour and HPV subtype. Repeated-measures analysis of variance will be used to test for between-group differences over time in Quality of Life scores. Analysis of covariance will be used to compare group scores on these outcomes at 20 weeks and at 12 months, with adjustment for baseline scores.

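### Randomisation is stratified by study centre but the primary logistic model leaves centre out, and with about three failures expected after LLETZ the model needs a small-sample fit

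*Protocol article*

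**What the plan says.** The Randomization section names two stratification factors. One is age, in three bands. The other is site: "Sampling will be stratified according to study centre". The Setting section says that the trial opens at one clinic and is meant to become multi-centre; it gives no number of sites.

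Statistical methods compares imiquimod with LLETZ by logistic regression, by intention to treat, and gives a closed list: "Covariates in this analysis are age at diagnosis, CIN grade, smoking and HPV-subtype". Centre is not on it. The recurrence model in the same section leaves centre out too. The article does not say how HPV subtype is grouped, and names no penalised or exact method.

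The design rates are in Sample size calculation: "The sample size calculation was based on a regression rate of 73 % at 20 weeks follow-up after immunotherapy", set against "a 95 % treatment efficacy of LLETZ". The result is 42 per arm, then "Allowing for a withdrawal rate of approximately 20 %, 53 women will have to be recruited in each arm". Recruitment is set higher, at 140 women or 70 per arm, and Interventions makes the allocation equal.

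**The concern.** There are two separate issues, and they pull in different directions.

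**Centre.** Stratified allocation balances the arms within centre. A model that ignores centre does not credit that balance, so its standard error is too large whenever centre predicts outcome. This could matter here because success rests on biopsies taken, and on histology and cytology read, at the sites. The article fixes the covariate list and includes one stratification factor but not the other, so this is a mismatch within the article and not a detail left open.

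**Few failures.** LLETZ is expected to succeed in 95% of women, so the odds ratio rests on a handful of LLETZ failures. Maximum-likelihood logistic regression is biased away from the null in such data, and it has no finite treatment estimate if one arm has no failures. At stake is a headline odds ratio that is somewhat exaggerated, or in a small share of possible trials cannot be reported.

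**Working it through.** **Inputs from the article.** Success 73% (imiquimod) and 95% (LLETZ), so failure 27% and 5%; 80% power; alpha 5%; withdrawal about 20%; 70 per arm; equal allocation. Sidedness is not stated; two-sided is assumed.

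**1. The plan's own figure.** Two proportions, pooled variance, no continuity correction, mean success 0.84:

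n = [1.960·√(2·0.84·0.16) + 0.842·√(0.73·0.27 + 0.95·0.05)]² / 0.22² = 42.4.

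The plan states 42, so it is reproduced to within rounding (rounding up gives 43). For withdrawal, 42/0.80 = 52.5, or 53 as stated. The sample size is not in dispute.

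**2. Expected failures.** Failures = n × 0.27 + n × 0.05. If 20% withdraw, 70 × 0.80 = 56 per arm remain.

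| Scenario | Imiquimod | LLETZ | Total |
|---|---|---|---|
| 70 per arm, 73% response | 18.9 | 3.5 | 22.4 |
| 56 per arm, 73% response | 15.1 | 2.8 | 17.9 |
| 70 per arm, 50% response | 35.0 | 3.5 | 38.5 |
| 56 per arm, 50% response | 28.0 | 2.8 | 30.8 |

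The 50% rows use the low end of the response range hypothesised under Study objectives and outcome measures. If withdrawals were instead counted as failures, the total would be 17.9 + 28 = 45.9.

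**3. Failures per coefficient.** Treatment plus four covariates is at least five slopes: 17.9/5 = 3.6 to 22.4/5 = 4.5. With HPV in four groups (assumed) there are seven: 2.6 to 3.2.

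**4. Chance of no LLETZ failure.** 0.95^70 = 2.8%; 0.95^56 = 5.7%.

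**5. Simulated logistic fits at the design rates.** The covariate odds ratios for failure are assumptions: CIN 3 2.0, smoking 1.5, HPV 16 2.0, age none. The true treatment odds ratio is (0.27/0.73)/(0.05/0.95) = 7.0 marginally, and 7.5 conditional on the covariates.

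| Per arm | Model | Bias in log OR | SD of log OR | Central 95% range of OR | Non-convergence |
|---|---|---|---|---|---|
| 70 | Unadjusted | – | 0.64 | 2.7–31.6 | 3.0% |
| 70 | Five slopes | 8.0% | 0.67 | 2.7–35.0 | 1.9% |
| 70 | Five slopes, Firth | 1.2% | 0.67 | 2.5–37.6 | 0% |
| 56 | Unadjusted | – | 0.66 | 2.3–28.2 | 6.1% |
| 56 | Five slopes | 7.7% | 0.73 | 2.3–37.0 | 5.6% |
| 56 | Five slopes, Firth | 0.5% | 0.74 | 2.2–50.1 | 0% |

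Coverage of the five-slope maximum-likelihood model was about 97%. Its power was 95% (70 per arm) and 85% (56 per arm), against 93% and 85% unadjusted. Firth fitting removes the bias and the failed fits; it does not narrow the range.

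With HPV in four groups, 19% (70 per arm) to 31% (56 per arm) of fits failed to converge, mostly in a covariate term. The treatment coefficient itself diverged in 2.6% to 6.2%, close to the chance of no LLETZ failure in step 4.

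**6. Leaving centre out.** Simulation under the null with 140 patients, four equal centres (assumed), allocation balanced within centre, and a between-centre SD of 0.5 or 1.0 on the logit scale. Rejection at nominal 5% was 3.7% and 3.3% without centre, and 4.6% in both cases with it. At 3,000 runs the Monte Carlo standard error is about √(0.046 × 0.954/3000) = 0.4 percentage points.

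**7. Adding centre as unpooled fixed effects.** Four centres give eight slopes: 17.9/8 = 2.2 to 22.4/8 = 2.8 failures per slope. With ordinary maximum likelihood, bias rose to 10.5% (70 per arm) and 13.7% (56 per arm), and non-convergence to 4.8% and 9.0%.

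**The case against.** The case for leaving the plan alone is substantial, and much of it stands.

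- **Centre may never matter.** With one site there is no term to add. Two independent readers, consensus, common criteria with p16 staining and specified biopsy sites all reduce centre differences, although central reading is not stated. Omission only makes the test mildly conservative. All of this stands and limits the size of the point, but it does not remove the mismatch in a trial meant to become multi-centre.
- **A reader might infer that five slopes on about 20 failures make the odds ratio unstable.** The figures do not support that. The range is nearly as wide with no covariates (2.7–31.6 against 2.7–35.0 at 70 per arm). The width comes from about three LLETZ failures.
- **A reader might infer that the treatment odds ratio becomes infinite once the LLETZ arm has no failure in some covariate level.** The listed model has main effects only, so this does not follow. With LLETZ failures of 3/35 and 0/35 in two levels of a covariate and imiquimod failures of 7/35 and 12/35, the fit converges with odds ratio 8.3 and standard error 0.65 on the log scale. On the LLETZ side, an infinite estimate is forced only by no failure in the whole arm.
- **Replacing the primary analysis with a risk difference** would be a choice between accepted methods. Sizing a trial on proportions and analysing it by logistic regression is routine.
- **HPV coding and the fitting method are commonly left to the analysis plan.** That is fair; their absence from the article is not held against it here. They enter the fix because adding centre to a sparse model makes them matter.

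**Conclusion.** The point holds as a modest improvement to the analysis, not as a threat to the trial's conclusion. The centre mismatch follows directly from the article's text. Its effect is a small loss of efficiency, about one percentage point of the nominal 5% under four assumed centres, and it arises only if further sites join and centre affects outcome.

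The failure counts follow from the article's own design rates. They imply about 8% overstatement of the log odds ratio under the assumed covariate effects, and a 2.8–5.7% chance that no finite treatment estimate exists. Failures rise to 31–39 if imiquimod response is 50%, but the LLETZ count, and so the chance of no LLETZ failure, stays the same.

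The documents do not support reading either issue as inflating false positives, or blaming the wide interval on the number of covariates.

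**What to change.** Keep logistic regression as the primary comparison and make these changes before outcome data are seen:

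- Add study centre to the primary covariate list, with small centres pooled by a stated rule or centre as a random intercept.
- Fix a coarse HPV grouping, for example type 16 against other.
- Name Firth penalisation or another small-sample method as the fitting method.
- Report alongside the odds ratio a risk difference with 95% confidence interval, stratified by the randomisation factors. It is on the scale used to size the trial and can be reported even if no LLETZ patient fails.

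The cost is analysis-plan wording and a few lines of code; recruitment, visits and patient management are untouched. The downside is sparsity: unpooled fixed centre effects would make the model worse, so pooling or a random intercept is part of the change. None of this narrows the interval much, because the number of LLETZ failures sets its width.

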**Methods/design:**

The study design is a randomized controlled trial. One hundred forty women with a histological diagnosis of high-grade CIN (CIN 2–3) will be randomized into two arms: imiquimod treatment during 16 weeks (experimental arm) or immediate LLETZ (standard care arm). Treatment efficacy will be evaluated by colposcopy with diagnostic biopsies at 20 weeks for the experimental arm. Successful imiquimod treatment is defined as regression to CIN 1 or less, successful LLETZ treatment is defined as PAP 1 after 6 months. Disease recurrence will be evaluated by cytology at 6, 12 and 24 months after treatment. Side-effects will be evaluated using a standardized report form. Quality of life will be evaluated using validated questionnaires at baseline, 20 weeks and 1 year after treatment. Biomarkers, reflecting both host and viral factors in the pathophysiology of CIN, will be tested at baseline with the aim of developing a predictive biomarker profile for the clinical response to imiquimod treatment.

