
Ideally, the response to imiquimod treatment of an individual patient would be predictable. Previous studies have shown that the natural behaviour of CIN lesions can be partially predicted by biomarker models, consisting of markers that reflect host, viral and cellular factors [4, 16]. This study aims to develop a similar biomarker prediction model for the individual response to imiquimod treatment, in order to enable individualized treatment of CIN lesions.

This study aims to confirm the short and long term efficacy of imiquimod 5 % cream in the treatment of high-grade CIN, as well as to evaluate clinical applicability by assessment of side-effects and quality of life during and after treatment. Additionally, it aims to develop a biomarker prediction model for clinical response to imiquimod treatment of high-grade CIN. For this purpose, we designed a randomized controlled trial with two arms, in which imiquimod treatment is compared to standard treatment by LLETZ. The trial was designed according to the CONSORT guidelines.

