## Discussion

The development of a non-invasive treatment modality for high-grade CIN lesions may diminish complications as a result of surgical intervention. An earlier study indicates that imiquimod induces disease regression in 73 % [7, 13]. Thus, imiquimod treatment may prevent surgical treatment in the majority of patients. The current study aims to test the treatment efficacy hypothesis as well as long term disease recurrence after treatment and clinical applicability of imiquimod treatment, defined as side effects and quality of life during and after treatment. Furthermore, it aims to develop a prediction model for clinical response to imiquimod treatment, based on histological biomarkers.

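### The biomarker model has no CIN grade term and does not settle whether HPV type is a candidate, so as written it cannot show what the markers add to grade.

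*Protocol article*

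**What the plan says.** The protocol article, Study objectives and outcome measures, makes the prediction of response to imiquimod a primary objective, and the Background says the model should allow treatment to be individualised.

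Statistical methods describes three logistic analyses:

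- **Efficacy:** "Covariates in this analysis are age at diagnosis, CIN grade, smoking and HPV-subtype".
- **Recurrence:** "after adjustment for age at diagnosis, CIN grade, smoking, sexual behaviour and HPV subtype".
- **Biomarker model:** "A biomarker prediction model for adequate response to imiquimod treatment will be developed by backward logistic regression analysis of biomarkers", with selection by likelihood-ratio tests. No clinical covariate is named.

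On which biomarkers are meant, the article points two ways. The Abstract (Methods/design) says "Biomarkers, reflecting both host and viral factors in the pathophysiology of CIN, will be tested at baseline", and the Background aims at a model like earlier ones "consisting of markers that reflect host, viral and cellular factors". The Discussion, however, describes the model as "based on histological biomarkers". The Data collection section lists 12 histological markers (five lymphoproliferative, seven cell-cycle) and shows HPV genotyping as a separate baseline item.

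The Interventions section bases the CIN diagnosis on differentiation, maturation, stratification and nuclear abnormality together with p16 staining. p16 is also one of the 12 markers.

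**The concern.** Entry is CIN 2 or CIN 3, and success is CIN 1 or less. A CIN 3 lesion must therefore fall two grades and a CIN 2 lesion one, so a difference in response by grade is plausible from the endpoint's definition alone. The plan itself treats grade as relevant to this endpoint by adjusting for it in the efficacy model.

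Some candidate markers probably carry the same information as grade. p16 is tied to the diagnosis by construction. Ki67, CK 13 and CK 14 plausibly reflect the proliferation and differentiation by which grade is read. In a model without grade, such a marker can be retained as a stand-in for something the pathologist has already reported.

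At stake is whether the panel is useful. Grade is known for every woman before treatment, so a panel that has not been set against grade gives no evidence that the extra staining helps to choose treatment.

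**Working it through.** **1. The plan's own figures.** No sample size is given for the biomarker model. The efficacy calculation (73% v 95%, 80% power, alpha 5%, taken as two-sided) reproduces closely. With pooled variance and mean proportion 0.84:

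n = [1.96 × √(2 × 0.84 × 0.16) + 0.842 × √(0.73 × 0.27 + 0.95 × 0.05)]² / 0.22² = (1.016 + 0.416)² / 0.0484 ≈ 42.4

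That is 43 rounded up, against 42 stated; 42 / 0.8 = 52.5 gives the stated 53. The present point does not depend on this.

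**2. Information for the biomarker model.** Inputs from Sample size calculation: 70 women in the imiquimod arm, 73% response, about 20% withdrawal (70 × 0.8 = 56).

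- Non-responders: 70 × 0.27 = 18.9; 56 × 0.27 = 15.1.
- Per candidate, 12 markers: 18.9 / 12 = 1.6; 15.1 / 12 = 1.3.
- With two terms added (14): 18.9 / 14 = 1.35; 15.1 / 14 = 1.08.

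**3. How often a stand-in marker is kept.** The following are assumptions, not in the documents: CIN 2 and CIN 3 equally frequent; overall response 73%; four of 12 markers shifted 1.25 SD between grades and eight unrelated to grade; no marker with any effect of its own; backward elimination by likelihood-ratio test with removal at 5%. There were 400 simulated trials per setting, so the simulation error is roughly 1 percentage point for the per-marker columns and 2.5 points for the last two.

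| Response CIN 2 / CIN 3 | n | Kept per tracking marker, no grade | Kept, grade forced in | At least one marker kept, no grade | At least one kept, grade forced in |
|---|---|---|---|---|---|
| 73% / 73% | 56 | 8% | 8% | 55% | 55% |
| 73% / 73% | 70 | 7% | 7% | 54% | 55% |
| 83% / 63% | 56 | 14% | 9% | 69% | 56% |
| 83% / 63% | 70 | 13% | 7% | 70% | 52% |
| 88% / 58% | 56 | 19% | 10% | 77% | 53% |
| 88% / 58% | 70 | 22% | 7% | 82% | 54% |

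Where response differs by grade, a tracking marker is kept in 13-22% of trials without grade and 7-10% with it. Where response does not differ, grade makes no difference.

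**4. Sensitivity to the marker-grade link.** When one marker is tested alone, the contrast is wider: 14-34% without grade (83% v 63%) or 25-62% (88% v 58%), against 5-6% with grade, for marker-grade correlations of 0.5 and 0.8. With equal grade groups a shift of d SD gives correlation (d/2) / √(1 + (d/2)²), so 1.25 SD corresponds to 0.625 / 1.179 = 0.53. The single-marker test is not the planned procedure; the table above is closer to it.

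**The case against.** The strongest reply has three parts.

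**The article is condensed.** It gives the biomarker model one sentence and does not say that grade is excluded or that added value will go unassessed. The full protocol or an analysis plan may say more. This limits the certainty. But the same section names the covariates of the two neighbouring models, so the wording shown does describe a model without grade.

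**The objective is prediction.** A marker that predicts through its link with grade still predicts, and the other two models list covariates for a different purpose. This stands in part: such a marker is not a false predictor of response. What remains unknown is its gain over grade, and that matters because the model is meant to guide individual treatment.

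**Selection noise is the larger problem.** This also stands. With grade forced in, 52-56% of simulated trials still keep at least one marker that has no effect.

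Three stronger readings are tempting and are not supported:

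- That HPV type is left out. The Abstract and Background count viral factors among the biomarkers; the Discussion and the layout of Data collection point the other way. The text is unclear, not exclusionary.
- That markers without added value will be reported as predictors. This needs response to differ by grade and markers to follow grade, and the documents give neither figure.
- That the trial could never answer the question. Baseline grade is established at entry and genotype is recorded, so the comparison remains possible; it is simply not in the stated analysis.

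**Conclusion.** The point holds in a limited form. As written, the biomarker model has no CIN grade term, and the role of HPV type is unresolved. The stated analysis therefore cannot show whether the panel improves on grade.

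Under the assumptions above, leaving grade out raises the chance of keeping a grade-tracking marker with no effect of its own from 7-10% to 13-22% per marker. The size rests on the assumed 1:1 grade split, the 20- or 30-point response gap and the 1.25 SD shift. It vanishes if response does not differ by grade, although the gain over grade would still be unreported. The change is worth making because it replaces the stated method with one that answers the practical question, using data already to hand.

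**What to change.** In Statistical methods:

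1. Start the biomarker analysis from a base model with baseline CIN grade (2 v 3) forced in.
2. State whether HPV type is a base term or a candidate marker, and bring the Abstract, Background, Data collection and Discussion into line.
3. Report the likelihood-ratio test and the change in c-statistic for the base model against the base model plus markers.
4. Reduce the 12 candidate markers in advance, or use penalised estimation.

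**Cost.** No new data are needed and trial conduct does not change. The base model uses one or two degrees of freedom when only about 15-19 non-responders are expected, which is why step 4 belongs with it. Forcing in grade does not by itself remove general selection noise.
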